## Discussion

Physicians strive to identify the most appropriate and effective cancer treatment for each individual patient. However, reliable evidence for precision oncology approaches to guide physicians in their therapy decisions is still scarce. Thus, there is an urgent need to provide more evidence to determine relevant drug/alteration associations [24].

Only about 5% of cancer patients participate in clinical trials [25], often due to strict inclusion criteria [26]. With the increasing number of molecularly defined patient groups, the overall prevalence of patients with such alterations becomes even smaller, which makes recruitment into trials even more challenging. However, the element of randomization is still a very important technique in clinical research to investigate patient benefits and harms. The SHIVA trial as well as the ongoing international CUPISCO trial (NCT03498521) [27] are strong examples for the feasibility of randomization in precision oncology trials, supporting the conduction of randomized controlled trials in this research field. The goal of these two examples is not to test a specific drug against a standard of care, but to compare the whole approach of testing and recommended treatment against standard of care. Nevertheless, it is also of great importance to understand current practice of precision oncology approaches outside clinical trials. One of the major challenges in the field of precision oncology is the standardization of testing methods, their interpretation and actual implication for clinical decision making. These are research fields that can preferably be investigated in cohort studies with very broad inclusion criteria. In addition, data on effectiveness can easily be explored for hypothesis generation and non-randomized comparative analyses. Thus, establishing a registry study such as INFINITY will provide complementary evidence to the complex field of precision oncology leveraging data that combine patient’s clinical characteristics, the tumor genotype together with the treatment journey and clinical outcomes in real-world.

The non-interventional design of the INFINITY study represents both a limitation, as it precludes causal conclusions on differences between subgroups, and a strength because it allows presentation of real-world data on patients not selected by restrictive inclusion criteria and on test rates in routine care. The retrospective documentation is a potential risk of bias for reporting patients with a better response to NSTT by participating sites. However, this was mitigated by defining certain time periods for documentation. A strength of this study is the enrollment from both hospitals and office-based oncologists in private practices all over Germany, recruiting a large, representative study cohort.

In summary, the INFINITY registry aims to provide real-world data, including the clinical outcomes, on molecular alteration-matched targeted therapies used outside of their approved indication in patients with advanced solid tumors or hematologic malignancies. Thus, the results will describe how precision oncology is currently applied and implemented in routine clinical practice in Germany. Furthermore, the results will complement available evidence on effectiveness of precision oncology in routine clinical practice in general, and of specific drug class/alteration matches used outside their approved indications.

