### Data collection

Study sites are asked to retrospectively document all patients who meet the eligibility criteria (including deceased patients) until 2023.

Clinical routine data documented by study sites is structured and transferred by the site staff into a secure web-based eCRF system (iostudy office). The iostudy office edc system is a fully validated secure software that conforms to 21 CRF Part 11 requirements. As source of documentation, routine medical records are used. Sites will document data regarding patient and disease characteristics (e.g. sex, entity, staging, histology) as well as treatment details of NSTT and prior and subsequent therapies applied. The investigator’s treatment decision process is evaluated using a paper-based questionnaire comprising questions on factors influencing treatment decisions as well as information on respective potentially actionable alteration including ESCAT levels, which are transferred into the eCRF. eCRF documentation will be checked for plausibility and completeness both centrally and on-site by data managers, medical managers, and clinical monitors, respectively.

Study sites send pseudonymized diagnostic reports (e.g. pathology reports, reports on sequencing results such as NGS) and molecular tumor board (MTB) reports, if applicable, including treatment recommendations to iOMEDICO. Dedicated and trained iOMEDICO staff extracts information from the reports and enters data on all reported immunohistochemistry or mutational profiling as well as molecular alterations including complex sequencing results (including test panels and further information) into a pre-specified electronic database. These data are documented as described in the report but in analogy with the HGVS (Human genome variation society) code for proteomic und genomic sequence variants [23]. Independent checks for consistency of data entries by a second reviewer are performed. This is to ensure central quality control for these comprehensive and complex data. This structured data capture enables standardized and structured analyses.

Additionally, we have established a decentral tissue sample biobank where information on tumor samples including contact details of local pathology departments is captured. This enables us to request samples for upcoming translational research projects.

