### Descriptive analyses

Regarding patient and disease characteristics as well as therapies applied, the following data will be analyzed:Patient and disease characteristics including e.g., sex, body mass index (BMI), Eastern Cooperative Oncology Group (ECOG) performance status, type of health insurance, comorbidities and tumors types, time from primary diagnosis to start of first NSTT, age at start of first NSTTDetails on NSTT including substance classes, treatment duration as well as prior and subsequent antineoplastic therapy lines

Characteristics regarding diagnostics and identified molecular alterations include the following:Frequencies: type of molecular diagnostic testing performed, proteins and genes tested, multigene panels or NGS in molecular diagnostics, type (by panel size) of NGS library sequenced, altered proteins and genes, if tested, treatment recommendations given in molecular diagnostic reports, implemented treatment recommendations given in molecular diagnostic reports, use of a MTB, implementation of the treatment recommendation given by MTBClinical decision making: Frequency of answers rated with a Likert scale on patient’s non-suitability for standard therapy options / choice of performed molecular diagnostics / choice of selected molecular target and targeted non-standard therapy / reasons for the selection of targeted non-standard therapy / primary goal of the non-standard targeted therapy / expected advantages of the non-standard targeted therapy and frequency of ESMO Scale of Clinical Actionability for molecular Targets (ESCAT) evidence levelsTurnaround times:◦ Duration from sample receipt to molecular testing result◦ Duration from molecular testing result to start of NSTT

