### Statistical analysis

No formal sample size calculation was performed. The sample size of 500 patients has been chosen to enable subgroup analyses for e.g., specific tumor entities with a predefined minimum number of patients. For example, given the distribution of patients for specific tumor entities from the MOSCATO trial [8], we expect 50 patients or more in each of the following cancer entities: head and neck cancer, gastrointestinal cancer, lung cancer, breast cancer und genitourinary cancer. Furthermore, given 100 recruiting sites with 1-2 eligible patients per year and 4 documentation periods, it can reasonably be expected to reach the sample size of 500 patients in time.

All patients fulfilling the eligibility criteria and with documented start date of NSTT will be included in the full analysis set (FAS). All variables will be analyzed in a descriptive manner. Categorical variables will be presented as absolute and relative frequencies and continuous variables as number of observations, median and range. Time-to-event variables (PFS and OS) will be analyzed using the Kaplan-Meier method. PFS is defined as the time from start of therapy to date of documented tumor relapse/progression or death due to any cause, whichever comes first. OS is defined as the time from start of therapy to date of death due to any cause. Patients with no event will be censored at the date of last contact or start of subsequent systemic therapy. The PFS ratio will be calculated to compare PFS of NSTT with time to progression (TTP) of preceding antineoplastic therapy for each patient. BOR is defined as best documented response achieved under NSTT. DCR is defined as proportion of patients who achieved complete response (CR), partial response (PR) or stable disease (SD) as best response; ORR is defined as proportion of patients who achieved either CR or PR as best response. TTR is defined as time from start of treatment to first objective response observed for patients who achieved a CR or PR. DOR is defined as time from documentation of tumor response to disease progression or death from any cause. TTF is defined as time from start of therapy to discontinuation of treatment for any reason, including progression, toxicity, and death.

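### Only patients who were tested and started a non-standard targeted therapy can enter the registry, so it cannot give the routine-care testing or implementation rates its text suggests

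*Protocol article*

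**What the plan says.** The Discussion presents the non-interventional design as both a limitation and a strength. The strength includes "real-world data on patients not selected by restrictive inclusion criteria and on test rates in routine care". The same section calls the cohort representative and concludes that "the results will describe how precision oncology is currently applied and implemented in routine clinical practice in Germany".

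The Methods fix who can be in the data:

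- Eligibility criteria: a patient must have begun or finished an NSTT prompted by a molecular finding, and the test results behind that decision must be available.
- Data collection: "Study sites are asked to retrospectively document all patients who meet the eligibility criteria (including deceased patients) until 2023".
- Statistical analysis: "All patients fulfilling the eligibility criteria and with documented start date of NSTT will be included in the full analysis set (FAS".

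Descriptive analyses lists the planned frequencies. They include "type of molecular diagnostic testing performed, proteins and genes tested, multigene panels or NGS in molecular diagnostics", use of a molecular tumor board (MTB), and two implementation items: one for recommendations in diagnostic reports and one for MTB recommendations.

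**The concern.** A rate in routine care needs a denominator of patients in routine care. For testing, that is everyone who could have been tested. For implementation, it is everyone who was given a recommendation. The registry has neither. A patient who was never tested, was tested but not treated, or had a recommendation that led to no NSTT cannot be included. The article describes no screening log or site-level count of such patients.

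Two things are at stake. First, the article states as a strength a property that its own eligibility criteria rule out. Second, the implementation frequencies appear without a stated denominator, next to a claim that a representative cohort will describe how precision oncology is implemented in Germany. A table built on treated patients could then be taken as the proportion of recommendations followed in practice.

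**Working it through.** The article states no testing or implementation rate, so there is no figure to reproduce. The check asks what the cohort can identify. The documents give none of the numerical inputs below. All are assumptions, chosen to show the range.

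**1. Any testing.** By eligibility, P(tested | included) = 1. This holds for every value of the true routine-care rate, so the observed 100% says nothing about that rate.

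**2. Implementation.** Take all patients given a recommendation for an NSTT. Let

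- a = share who receive the recommended NSTT (the routine-care implementation rate),
- b = share who receive a different NSTT,
- 1 − a − b = share who receive no NSTT and so never enter.

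The share in the cohort is a/(a + b). Because a + b ≤ 1, it is never below a.

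| True rate a | b = 1% | b = 5% | b = 10% |
|---|---|---|---|
| 10% | 91% | 67% | 50% |
| 20% | 95% | 80% | 67% |
| 40% | 98% | 89% | 80% |
| 60% | 98% | 92% | 86% |

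Example: a = 10%, b = 1% gives 0.10/0.11 = 91%. A cohort share of 80% appears twice, for true rates of 20% and 40%.

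**3. The same in reverse.** Let F = a + b, the share of patients with a recommendation who get any NSTT. Then a = cohort share × F. For a cohort share of 80%:

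- F = 5%: a = 0.80 × 0.05 = 4%
- F = 50%: a = 0.80 × 0.50 = 40%
- F = 100%: a = 80%

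F cannot be learned from the registry, so a cannot either.

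**4. Type of test.** Shares of particular tests vary within the cohort, but they too are conditional on treatment. Let q be the share of NGS among all tested patients, and r the ratio of the chance of an NSTT after NGS to the chance after other tests. The cohort share is qr/(qr + 1 − q). With q = 30%:

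- r = 1: 30%
- r = 2: 0.6/1.3 = 46%
- r = 4: 1.2/1.9 = 63%

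The share among treated patients is a valid description of treated patients. It equals the share among all tested patients only if r = 1.

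**The case against.** The strongest reply has four parts.

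*Test rates may mean only how often particular tests were used.* Descriptive analyses lists types of test, genes and panels, and does not list any-testing as an output. These frequencies are estimable and not fixed at 100%. That stands, and a reader who inferred that nothing about testing or implementation can be estimated would go too far. But the Discussion ties the claim to routine care, and step 4 shows that even these frequencies need the restriction to treated patients.

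*The quoted sentence says nothing about implementation.* Correct. The implementation point rests on the two listed frequencies, together with the general closing statement on how precision oncology is implemented. No sentence in the article presents either frequency as a population rate, so this part asks for a definition and does not correct a false statement.

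*The conditioning is already disclosed.* The objectives, eligibility criteria and analysis set all say that patients received an NSTT, and an output such as "Duration from molecular testing result to start of NSTT" carries its own condition. That is a fair answer for the turnaround and gene-frequency outputs, which need no change. It does not rescue a claimed strength that contradicts the disclosed condition.

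*An article condenses the protocol.* True, but the point does not concern an omitted detail. The article makes a positive claim that its own criteria exclude. The selection risk it does acknowledge is sites preferring to report better responders, which is a different matter.

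**Conclusion.** The concern holds in a limited form. The routine-care testing rate cannot be estimated, and neither can the rate at which report or MTB recommendations are carried out among all patients who receive one. What can be estimated, among NSTT-treated patients, is the distribution of test types, genes tested and NGS or MTB use, and the concordance of the given NSTT with the recommendation.

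That concordance is at or above the routine-care rate. On the assumed inputs, a true rate of 10% would show as 50% to 91%, and a true rate of 40% as 80% to 98%. The size of the gap is not identifiable from the data. The direction assumes that implementation means giving the recommended NSTT outside a clinical trial, since trial treatment is an exclusion criterion, and that sites document concordant and discordant patients equally completely.

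A reader might infer three stronger things that the documents do not support:

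- That observed implementation is forced to 100%. It is not, because a treated patient may have received an NSTT other than the one recommended.
- That particular reasons explain the missing untreated patients. The article gives none.
- That the path from result to treatment will look faster than it is. Patients who never start have no such interval, so the direction depends on how they would be counted.

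The effectiveness outcomes and the analysis set are not affected by this point. It is worth correcting because a headline strength is wrong as written.

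**What to change.** 1. In the Discussion, delete the part of the strength that refers to test rates, or restrict it to frequencies of test types among NSTT-treated patients.
2. In Descriptive analyses, define the two implementation outputs as concordance of the administered NSTT with the diagnostic-report recommendation and with the MTB recommendation, each among treated patients.
3. In the limitations, state that routine-care testing and implementation rates are not estimable, because patients who were untested, or who had a recommendation but no NSTT, are not captured.

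The cost is a few sentences, with no new data and no change of analysis. Keeping the claim as it stands would instead need site-level counts of all patients who could have been tested, and of all who received a recommendation. That would be new data collection.

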## Data Availability

The datasets used and/or analyzed during the current study are available from the corresponding author on reasonable request.

## Abbreviations

BOR: Best overall response
BRAF: v-raf murine sarcoma viral oncogene homolog B1
BRCA1/2: Breast cancer 1/2
DCR: Disease control rate
dMMR: Mismatch repair deficient
DOR: Duration of response
ECOG: Eastern Cooperative Oncology Group
eCRF: Electronic case report form
ERBB2: Erb-b2 receptor tyrosine kinase 2
FAS: Full analysis set
FDA: Food and Drug Administration
FISH: Fluorescent in situ hybridization
FLT-3: FMS-like tyrosine kinase-3
HER2: Human epidermal growth factor receptor-2
HGVS: Human genome variation society
IHC: Immunohistochemistry
MSI-H: Microsatellite instability-high
MTB: Molecular tumor board
NGS: Next generation sequencing
NSTT: Non-standard targeted therapy
NTRK: Neurotrophic tyrosine receptor kinase
ORR: Overall response rate
OS: Overall survival
RT-PCR: Reverse transcription polymerase chain reaction
PD-L1: Programmed death-ligand 1
PFS: Progression-free survival
RET: Rearranged during transfection
TMB-H: High tumor mutational burden
TTF: Time to treatment failure
TTR: Time to response
